| DURATION OF SUBJECT PARTICIPATION AND DURATION OF STUDY | 
Subjects will be on study for up to 2 months
 
Screening: 2-4weeks
 
Treatment: 1day
 
Follow-up: 1day, 1week and1month (1 month in total)
 
The total duration of the study is expected to be 9 months.
                                                                                                                                                                                                                                                                                                                                                                                                                                                                                                                                                                          |
| STATISTICS PLAN                                         | 
Data were analyzed using SPSS 19.0 software (SPSS, Chicago, IL, USA). Paired samples t-test (normally distributed data) or Wilcoxon test (non-normally distributed data) was used to determine significant differences between pre- and post-operative measurements in each group. Comparisons between the two groups were performed by Independent samples t-test (normally distributed data) or Mann-Whitney U test (non-normally distributed data). Pearson or Spearman rank correlation was used to analyzed for the correlations between tear inflammatory mediators and ocular surface parameters. P value of less than 0.05 was considered statistically significant. Data are presented as mean <math>\pm</math> SD.
                                                                   |

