## **2 STUDY RATIONALE**

This first all-in-one FS-laser system was designed to perform the refractive lenticule extraction (ReLEx) procedures, femtosecond lenticule extraction (FLEx) and small-incision lenticule extraction (SMILE). In FLEx, a corneal flap is created by the FS laser (similar to LASIK) and lifted, allowing lenticule removal[1-3]. For SMILE, a truly flapless procedure, only a small—2-4mm—incision is made, through which the lenticule is removed. Multiple etiologies contribute to this ocular surface disruption, including the flap creation and stromal ablation involved in previous refractive surgery techniques, such as: disable tear film, damage of the corneal nerve and postoperative inflammatory mediator. For both FLEx and SMILE, stromal ablation has been replaced by refractive lenticule removal. In terms of corneal flap formation, FLEx still requires an epithelial-stromal flap, while SMILE employs only a small incision to extract the lenticule. Hence, we hypothesize that SMILE will have less effect on patients' ocular surface markers and inflammatory mediators, compared to FLEx. To test our hypothesis, we conducted a prospective clinical study in patients who underwent FLEx or SMILE. Ocular surface parameters and inflammatory mediators were assessed and compared between the different types of surgery.

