### **2.1.2 Risk of overcorrections or undercorrections**

We will make a appropriate surgery strategy according to patients' refractive status, best corrected visual acuity and demands.

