## **4 STUDY DESIGN**

This is a single center, prospective and non-randomly study. 41 patients are planned to be enrolled. They are divided into two groups. One group will undergo the FLEx surgery, the other group will undergo the SMILE surgery. The ocular surface parameters and concentration of tear inflammatory mediators will be assessed at baseline, 1 day,1 week and 1 month postoperatively. Subjects who meet all inclusion criteria and none of the exclusion criteria will be entered into the study.

1. Minimum age of 18 years(range from 18 year to 25 years).
2. Corneal thickness more than 500  $\mu\text{m}$  and calculated residual stromal bed after treatment greater than 300  $\mu\text{m}$ .
3. Corneal thickness more than 500  $\mu\text{m}$  and calculated residual stromal bed after treatment greater than 300  $\mu\text{m}$ .
4. Preoperative cylindrical equivalent refraction between -0.25 D and -1.50 D.
5. Preoperative corneal curvature from 41.0 D to 46.0 D with a regular topographic pattern.

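### The non-randomised SMILE versus FLEx comparison rests on unadjusted two-sample tests, so pre-operative differences between the groups can be counted as an effect of surgery

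*Protocol*

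**What the plan says.** - **Design.** Section 4 (Study Design): "This is a single center, prospective and non-randomly study". The same section continues: "41 patients are planned to be enrolled. They are divided into two groups". It gives no group sizes, assignment rule, matching or stratification.
- **Hypothesis.** Section 2 (Study Rationale): "Hence, we hypothesize that SMILE will have less effect on patients' ocular surface markers and inflammatory mediators, compared to FLEx". The groups are defined by the operation received: "To test our hypothesis, we conducted a prospective clinical study in patients who underwent FLEx or SMILE".
- **Between-group analysis.** Protocol synopsis, Statistics Plan: "Comparisons between the two groups were performed by Independent samples t-test (normally distributed data) or Mann-Whitney U test (non-normally distributed data"). No covariate, regression model, matching or propensity method is named.
- **Use of baseline.** In the same place, the paired t-test or Wilcoxon test "was used to determine significant differences between pre- and post-operative measurements in each group". This is the only stated use of the baseline values in testing.
- **Eligibility.** Section 5.2 limits age, corneal thickness, residual bed, cylinder and curvature. Criterion 3 repeats criterion 2, and no spherical range appears. Section 2.1.3 refers to high, medium and low myopia.

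**The concern.** In a randomised trial, an unadjusted two-sample test is valid, if sometimes inefficient, because the groups differ before surgery only by chance. Here nothing protects against systematic pre-operative differences, and the analysis does not deal with them either. They can enter in two ways:

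1. **The outcome's own baseline.** If one group starts with, say, lower tear secretion, part or all of that gap will still be there after surgery.
2. **Another prognostic factor.** Degree of myopia is the clearest candidate. Eligibility does not restrict it, and it bears on how much tissue the lenticule removes.

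The between-group sentence also leaves the analysed quantity open. The objectives in section 3.1 speak of changes, but the test could equally be run on post-operative values. The two choices react differently to a baseline imbalance, so the size and even the direction of the bias depend on a decision that the plan does not make. What is at stake is the study's main conclusion, that SMILE has less effect than FLEx.

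**Working it through.** The protocol gives no effect size, SD, power or group split, so none of its figures can be reproduced. The calculation below shows scale only.

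**Inputs**
- From the documents: total N = 41 (section 4) and significance level 0.05 (Statistics Plan).
- Assumed: split 20/21, two-sided test, equal SDs set to 1, normal data, no true surgical effect, correlation r = 0.6 between baseline and follow-up, and a baseline group difference d of 0.5 or 0.8 SD.

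**Standard error of a group difference:** √(1/20 + 1/21) = 0.312 SD, with 39 degrees of freedom. The rejection rate comes from the noncentral t distribution with noncentrality = (expected difference in SD units) / 0.312.

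Two models are plausible for how an imbalance carries forward without any surgical effect:
- **Model A, regression to the mean:** the expected post-operative difference is r·d.
- **Model B, stable difference:** the expected post-operative difference is d.

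**t-test on post-operative values**
- A, d = 0.5: 0.6 × 0.5 = 0.30 SD; 0.30/0.312 = 0.96; false positives 15.5%.
- A, d = 0.8: 0.6 × 0.8 = 0.48 SD; 0.48/0.312 = 1.54; false positives 32.3%.
- B, d = 0.5: 0.50/0.312 = 1.60; false positives 34.5%.

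**t-test on change.** The SD of change is √(2(1 − 0.6)) = 0.894.
- A, d = 0.5: expected difference (0.6 − 1) × 0.5 = −0.20; 0.20/0.894 = 0.224 SD of change; noncentrality 0.224/0.312 = 0.72; false positives 10.7%.
- A, d = 0.8: −0.32; 0.32/0.894 = 0.358; noncentrality 1.15; false positives 20.1%.
- B: expected difference 0; false positives 5%.

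**ANCOVA on baseline (simulation)**
- A: bias 0; false positives about 5% at both imbalances.
- B: bias (1 − 0.6) × d, which is 0.20 SD at d = 0.5 and 0.32 SD at d = 0.8; false positives about 12% and 21%.

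| r = 0.6, no surgical effect | A, 0.5 SD | A, 0.8 SD | B, 0.5 SD | B, 0.8 SD |
|---|---|---|---|---|
| Post-operative t-test | 15.5% | 32.3% | 34.5% | 70.4% |
| Change-score t-test | 10.7% | 20.1% | 5% | 5% |
| Baseline ANCOVA | 5% | 5% | 12% | 21% |

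**A separate confounder**, such as degree of myopia. The bias is its imbalance multiplied by its correlation with the analysed outcome.
- Imbalance 0.5 SD, correlation 0.3: 0.15 SD; 7.5% false positives.
- Imbalance 1.0 SD, correlation 0.7: 0.70 SD; 59% false positives.

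This holds whether the analysed outcome is the post-operative value or the change, so change scores do not remove it.

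**The case against.** **The documents show no imbalance, and the design narrows the room for one.** Age is 18 to 25. Cylinder, curvature and corneal thickness are bounded. Tear-supplement users and recent contact lens wearers are excluded, and section 2.1.1 excludes existing dry eye. One surgeon operates, and post-operative drops are common to both groups. This stands: nothing in the protocol makes 0.5 or 0.8 SD typical. It does not replace adjustment, because these limits leave sphere open and do not equalise baseline outcomes.

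**The test may be meant for changes.** The objectives point that way, and under a stable difference a change score holds 5%. This too stands as far as it goes. But the plan does not say so, change scores fail under regression to the mean, and a separate confounder remains.

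**A statistical analysis plan may cover this.** Much modelling detail can properly sit there. However, the protocol itself names the between-group tests, so the point concerns what is stated.

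A reader might also infer more than the documents support:
- *That patients chose their operation.* Section 2.1.2 says "We will make a appropriate surgery strategy according to patients' refractive status, best corrected visual acuity and demands", but this concerns over- and undercorrection and is not an allocation rule. The text supports only non-randomised groups with no stated rule.
- *That the plan infers a group difference from significance in one group and not in the other.* It does not; it plans a direct two-group test, and the paired tests serve the stated objective of pre- to post-operative change.
- *That every useful covariate is already study data.* Baseline outcomes are scheduled in section 4. Spherical equivalent and lenticule thickness are not listed among the assessments.

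**Conclusion.** The point holds in a limited form. The only stated test of the comparative hypothesis is unadjusted, in a non-randomised study with no assignment rule and with the analysed quantity undefined. Pre-operative differences *can* therefore be attributed to surgery; the documents do not show that they will be.

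On the assumptions above, a 0.5 SD baseline imbalance lifts the nominal 5% error of a post-operative comparison to about 15% (regression to the mean) or 35% (stable difference). The exception is a stable difference in the outcome itself that is analysed as change, where the error stays at 5%. The split, imbalances and correlations are all assumed, and the figures are for the t-test, not the Mann-Whitney test.

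It is tempting to conclude that baseline ANCOVA always repairs the comparison and that change scores always over-correct. That is true only under regression to the mean. If the difference is stable the ranking reverses, and nothing in the protocol says which model applies. Adjustment is better than none, but it does not turn this design into a randomised comparison.

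**What to change.** In the Statistics Plan, replace the between-group sentence with the following:

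1. **Main comparison.** For each outcome, a baseline-adjusted comparison at each post-operative visit at which it is measured. Use ANCOVA by visit, or a mixed model with surgery, visit, surgery × visit and the outcome's baseline value. Use a rank-based version for fluorescein staining and corneal sensitivity, which are scored in coarse steps.
2. **Confounder.** Add pre-operative spherical equivalent as a covariate, taken from the surgical work-up and listed as study data. With 41 patients, keep the covariate list this short.
3. **Reporting.** Give the adjusted SMILE minus FLEx difference with its 95% CI as the test of the hypothesis.
4. **Sensitivity analysis.** Prespecify a change-score comparison, because baseline ANCOVA is biased if the group difference is stable.
5. **Interpretation.** Describe how patients came to be in each group, and word the result as an association.
6. **Paired tests.** Keep them for the within-group objective, but do not use them as evidence of a difference between the operations.

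The cost is mainly wording, recording of spherical equivalent, and slightly more analysis work. The two covariates use two degrees of freedom; a mixed model also spends some on visit and interaction terms. Baseline outcome values are already scheduled. If there is no imbalance, baseline adjustment at r = 0.6 reduces the standard error from 0.312 to about 0.312 × √(1 − 0.6²) = 0.25 SD.

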## **7 STUDY PROCEDURES AND GUIDELINES**

All patients provided written consent to participate in the study and finished all postoperative follow-up visits. All surgeries were performed by the same experienced surgeon ([name]) following standard procedures under topical anesthesia. One eye of each subject was selected randomly for statistical analysis.

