## **7.3 Clinical Assessments**

### **7.3.1 Corneal Central Sensitivity (CCS)**

Corneal central sensitivity is measured with a Cochet-Bonnet esthesiometer (Luneau, Paris, France). This instrument consists of a nylon monofilament that is 60 mm in length and with diameter of 0.12 mm. The instrument is advanced perpendicular to the central surface of the cornea until contact between the instrument and the cornea is made. If the patient feels the filament, the response is defined positive. Corneal central sensitivity is tested three times with each filament length, and the length of the filament is sequentially reduced from 60 mm in 5-mm steps. At least two positive responses among three attempts are considered a positive result at each filament length. The longest filament length that resulted in a positive result is considered the corneal threshold. This evaluation will just be performed at baseline, 1 week and 1 month after surgery in order to avoid the potential for corneal damage at 1 day postoperatively.

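### The Statistics Plan names no between-group analysis that uses the baseline and the repeated post-operative visits together, so it provides neither an overall FLEx versus SMILE contrast nor a test of whether the difference changes by visit

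*Protocol*

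**What the plan says.** The only statistical text is the Statistics Plan row of the Protocol Synopsis. Within each surgery group, a paired t-test or Wilcoxon test "was used to determine significant differences between pre- and post-operative measurements in each group". Between groups: "Comparisons between the two groups were performed by Independent samples t-test (normally distributed data) or Mann-Whitney U test (non-normally distributed data". Pearson or Spearman correlations link mediators to ocular surface parameters. The threshold is that a P "value of less than 0.05 was considered statistically significant". No repeated-measures model and no per-patient summary over visits is named, and the row does not say whether the two-sample tests use raw values or changes.

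The data are longitudinal. Section 4 (Study Design) says that the ocular surface parameters and mediators "will be assessed at baseline, 1 day,1 week and 1 month postoperatively". Sections 7.3.1 (corneal central sensitivity, CCS) and 7.3.3 (fluorescein staining, FL) drop the day-1 measurement: "This evaluation will just be performed at baseline, 1 week and 1 month after surgery". Of the twelve measures in the primary objective, ten therefore have three post-operative values and two have two. On size, "41 patients are planned to be enrolled", and "They are divided into two groups. One group will undergo the FLEx surgery, the other group will undergo the SMILE surgery"; group sizes are not given. Section 7 adds that "One eye of each subject was selected randomly for statistical analysis", so the visits are the only source of repeated values within a patient.

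**The concern.** The hypothesis in Section 2 is that SMILE disturbs the ocular surface and tear mediators less than FLEx does. It singles out no visit. The paired tests look at one group and two time points and do not compare the surgeries. The two-sample tests compare the surgeries but take one value per patient. On this schedule their natural use is visit by visit, which makes up to 10 × 3 + 2 × 2 = 34 between-group tests.

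Three things are then lacking between groups: one answer per outcome that draws on all post-operative visits, a formal test of whether the surgery difference changes between visits, and any stated use of the baseline value. The last matters more here because the groups are not randomised. With 41 patients, precision is limited, and the repeated values are already being collected.

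**Working it through.** The protocol gives no effect size, SD, correlation or power figure, so there is no stated figure to reproduce. What follows rests on assumptions, each marked.

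**Inputs from the protocol.** N = 41; k = 3 post-operative visits for ten outcomes and k = 2 for CCS and FL; threshold 0.05.

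**Assumed.** Two-sided testing, a 21/20 split, equal variances across visits, and the correlations shown below.

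**1. Change from baseline, all visits equally correlated at r (variance 1).**
- Variance of one change: 2(1 − r). Covariance of two changes that share a baseline: 1 − r. Their correlation is therefore 0.5, whatever r is.
- SE of the visit-averaged contrast relative to one visit: √[(1 + (k − 1) × 0.5)/k].
- k = 3: √(2/3) = 0.816, an 18.4% smaller SE. k = 2: √(3/4) = 0.866, 13.4% smaller.
- As equivalent sample size: 41 × 3/2 ≈ 61 and 41 × 4/3 ≈ 55 patients.

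**2. Raw post-operative values, common correlation r.** The ratio is √[(1 + (k − 1)r)/k].

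| r | SE reduction, k = 2 | SE reduction, k = 3 |
|---|---|---|
| 0.3 | 19.4% | 27.0% |
| 0.5 | 13.4% | 18.4% |
| 0.8 | 5.1% | 6.9% |

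**3. Baseline-adjusted values, common correlation r.** The ratio is √{[(1 + (k − 1)r)/k − r²]/(1 − r²)}. For r from 0.3 to 0.8 the reduction runs from 21.6% to 15.0% (k = 2) and from 30.2% to 20.7% (k = 3).

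**4. Unequal correlations.** Surgery falls between baseline and follow-up, so post-operative visits may resemble each other more than they resemble baseline. Let them correlate at p with each other and at b with baseline. Two changes then correlate at (1 + p − 2b)/[2(1 − b)].
- p = 0.8, b = 0.3: 1.2/1.4 = 0.857. SE ratio 0.951 (k = 3) and 0.964 (k = 2), a reduction of about 5% and 4%.
- p = 0.5, b = 0.1: 1.3/1.8 = 0.722. SE ratio 0.903 and 0.928, a reduction of about 10% and 7%.

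**5. Illustrative power (noncentral t, 21/20, correlation of changes 0.5).**

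| True difference (SD of change) | Single visit | Visit average |
|---|---|---|
| 0.7 at every visit | 59% | 76% (k = 3), 71% (k = 2) |
| 0.9, 0.6, 0.3 at day 1, week 1, month 1 | 80%, 46%, 15% | 63% (k = 3) |

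In the second row the mean difference is (0.9 + 0.6 + 0.3)/3 = 0.6 SD. The average beats the two later visits but loses to day 1.

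**The case against.** The named tests are valid at each visit, and nothing in the protocol contradicts itself on this point. That stands: the issue is efficiency and completeness, not error.

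A reader might infer that the averaged contrast is 13-18% more precise as a matter of fact. The documents do not support this. The figure needs equal correlations, which the protocol nowhere gives; steps 2 and 4 of the working show how far it can move. It also describes change scores, whereas step 3 describes a baseline-adjusted analysis.

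A reader might also infer that the overall contrast is never estimated. The statistical analysis plan is not at hand, so one can say only that the protocol's Statistics Plan does not provide for it. Visit-by-visit testing is likewise the natural reading, not a stated rule.

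Nor does the hypothesis ask for an average over the early period. It names no visit and no period. The average is a different estimand from the visit-specific differences. It pools day 1 and week 1 with month 1, although Section 6 has scheduled drops in the first week and only as-required artificial tears afterwards. Making the average the sole or lead result would therefore be a choice with a cost.

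Finally, replacing every separate test would do harm. The within-group pre/post tests serve the primary objective, and the rank-test option protects outcomes that are bounded or may be skewed: Schirmer (0-30 mm), OSDI (0-100) and the tear concentrations. Both should stay.

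What remains is that the plan does not leave the method open. It names specific tests, and none of them uses the baseline and the repeated visits together to compare the surgeries. A smaller SE does not remove confounding from non-random allocation, but that is no reason to leave the collected data unused.

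**Conclusion.** The point holds as a gap in the protocol's Statistics Plan: for a design with a baseline and two or three post-operative values per patient, it offers no joint between-group analysis, no overall contrast and no surgery-by-visit test.

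The likely gain is real but uncertain. On change scores it is 18% (three visits) or 13% (two visits) in SE under equal correlations, and about 4-5% if post-operative visits correlate at 0.8 with each other and 0.3 with baseline. On raw values it is about 5-27% for correlations of 0.3-0.8. The power gain depends on a reasonably sustained effect; if the effect fades, it is lost relative to day 1. No sample-size figure is shown to be wrong.

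**What to change.** In the Statistics Plan:

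- Keep the within-group pre/post tests as they are.
- For the between-group comparison of each outcome, add a repeated-measures model with surgery, visit, surgery × visit and baseline value, and a within-patient covariance structure. The mixed-model procedure in SPSS is enough.
- Report both the surgery contrast averaged over post-operative visits and the visit-specific contrasts from the same model. State that the average covers three visits for ten outcomes and two for CCS and FL.
- Transform skewed outcomes, such as tear concentrations, where needed. For CCS, FL and any other outcome that remains non-normal, use a rank test on each patient's mean post-operative change.

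The cost is a few sentences of text and a little more analysis, with no new data or patients. The downside is that an effect confined to one visit is diluted in the average, which is why the visit-specific contrasts are reported beside it.

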| PRIMARY OBJECTIVE     | Determine the changes of central corneal sensitivity, Schirmer I test (SIT), noninvasive tear breakup time (NI-TBUT), tear meniscus height, corneal fluorescein (FL) staining, ocular surface disease index (OSDI) and tear concentrations of interleukin-1 $\alpha$ (IL-1 $\alpha$ ), tumor necrosis factor- $\alpha$ (TNF- $\alpha$ ), nerve growth factor (NGF), interferon- $\gamma$ (IFN- $\gamma$ ), transforming growth factor- $\beta$ 1 (TGF- $\beta$ 1) and matrix metalloproteinase-9 (MMP-9) of the two surgeries preoperatively and postoperatively.                                                                                                                                                                                                                                                                                                                                                                                                                                                                                                                                                                                                                                                                                                                                                                                                     |

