| NUMBER OF SUBJECTS    | 41 patients in total                                                                                                                                                                                                                                                                                                                                                                                                                                                                                                                                                                                                                                                                                                                                                                                                                                                                                                                                                                                                                                                                                                                                                                                                                                                                                                                                                  |

|                                                                |                                                                                                                                                                                                                                                                                                                                                                                                                                                                                                                                                                                                                                                                                                                                                                                                              |

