### **3.2 Secondary Objective**

Determine the correlation between inflammatory mediators and ocular surface changes.

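### The only secondary objective tests 36 mediator-by-surface pairs at a blanket P<0.05 with no lead pair; with no true association, one grid yields a false link about 45–84% of the time

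*Protocol*

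**What the plan says.** Section 3.2 of the protocol gives one secondary objective: "Determine the correlation between inflammatory mediators and ocular surface changes". The Statistics Plan in the synopsis provides the method: "Pearson or Spearman rank correlation was used to analyzed for the correlations between tear inflammatory mediators and ocular surface parameters". The significance rule that follows covers all analyses alike: a P "value of less than 0.05 was considered statistically significant".

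The variables come from the primary objective (synopsis and section 3.1). The six surface measures are corneal sensitivity, Schirmer I, non-invasive breakup time, tear meniscus height, fluorescein staining and OSDI. The six mediators are IL-1α, TNF-α, NGF, IFN-γ, TGF-β1 and MMP-9. The sample is "41 patients in total", with one eye per patient analysed (section 7).

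On timing, section 4 states: "The ocular surface parameters and concentration of tear inflammatory mediators will be assessed at baseline, 1 day,1 week and 1 month postoperatively". Sections 7.3.1 and 7.3.3 narrow this for corneal sensitivity and fluorescein staining: "This evaluation will just be performed at baseline, 1 week and 1 month after surgery". Neither is measured at 1 day.

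The protocol names no lead mediator, surface measure or visit for the correlations. It does not say whether they are pooled over the two surgeries or run within each.

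**The concern.** A single 5% threshold controls error for one test. Here the same threshold applies to every cell of a 6 × 6 grid, and nothing in the protocol's own rule separates a pair chosen in advance from one that stands out by chance. With 41 pooled patients, an observed correlation just above 0.31 in absolute value is enough for significance.

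At stake is how the secondary objective is read, that is, which mediators are said to go with which surface changes. These correlations are a separate family from the tests of SMILE against FLEx. Controlling multiplicity in the between-surgery comparisons would leave this family as it is.

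**Working it through.** The protocol gives no family-wise error rate, test count or power for the correlations, so there is no stated figure to reproduce.

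**Inputs.** Per-test level 0.05 (Statistics Plan; two-sided is assumed, and the family-wise rate depends only on the 0.05). Six mediators and six surface measures (section 3.1). n = 41 (synopsis). Visits from sections 4, 7.3.1 and 7.3.3.

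**Count of tests.**
- One full grid: 6 × 6 = 36.
- At 1 day, with two surface measures not taken: 6 × 4 = 24.
- Changes from baseline at the three postoperative visits: 24 + 36 + 36 = 96.

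**Critical correlation, 41 pooled patients.** r = t / √(n − 2 + t²). With 39 degrees of freedom t = 2.023, so r = 2.023 / √(39 + 4.09) = 0.308.

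**Independent tests, no true association.** The chance of at least one false positive is 1 − 0.95^m:
- m = 36: 1 − 0.95^36 = 84.2%
- m = 96: 1 − 0.95^96 = 99.3%

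**Expected number of false positives.** This is 0.05 × m whatever the correlation among the measures: 0.05 × 36 = 1.8, and 0.05 × 96 = 4.8.

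**Correlated measures.** Mediators probably correlate with one another, and so do surface measures, which lowers the family-wise rate. The documents give no such correlations, so a range is assumed. Pearson tests were simulated with n = 41, 3,000 to 4,000 data sets per setting, no association between the two sets, and equal correlation within each set. The correlation across visits was set to the same value or to 0.5. Separate runs agree to within about two percentage points.

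| Assumed correlation within each set | One grid (36 tests) | Three postoperative visits (96 tests) |
|---|---|---|
| 0 | 84% | 99% |
| 0.3 | 78–79% | 98% |
| 0.5 | 64–66% | 94% |
| 0.7 | 45–47% | 77–79% |
| 0.8 (extreme) | 35% | 69% |

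At an assumed 0.7, one grid still carries about nine times the nominal rate (45 / 5 = 9).

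**With the fix.** In simulation under the same null, Benjamini-Hochberg at 5% over the whole family brought the chance of any false claim to 5% or less, within simulation error, in every setting. For a 36-pair family, a pair that passes alone would need P ≤ 0.05 / 36 = 0.00139. At n = 41 that is an absolute correlation of about 0.48 instead of 0.31.

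**The case against.** **A statistical analysis plan may deal with it.** The choice of lead pair, visits and error control is often left to that document, and its absence here would be no fault on its own. That stands. But the protocol has its own Statistics Plan, which sets P<0.05 as the rule for the correlations along with everything else. The point rests on that stated rule.

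**A false link is near certain.** A reader might infer this, but the documents do not support it for the grid they define, where the rate is 84% at most and falls as the measures correlate. It approaches certainty only if the grid is repeated over visits, and the plan does not say that it will be.

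**There are 132 tests.** Counting all four visits gives 6 × 4 × 4 + 6 × 2 × 3 = 132. Section 3.2, however, speaks of changes in the ocular surface, and there is no change from baseline at baseline. Removing that grid leaves 132 − 36 = 96 at most for one pooled analysis.

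**The figures assume that nothing is associated.** Correct. Section 1 treats mediator fluctuations as important to surface damage, so the authors expect some real links. If some pairs are truly associated, the expected false links shrink to 0.05 times the number of null pairs. If half of the 36 were null, for example, that is 0.05 × 18 = 0.9. The problem becomes smaller but remains.

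**The 0.31 threshold assumes pooling.** Also correct. With about 20 patients per group (an assumption, since the split is not given) the critical value is about 0.44. This does not lower the error rate: one grid at n = 20 simulates at 85%, 79% and 65% for correlations of 0, 0.3 and 0.5. Two groups would make 2 × 36 = 72 tests at one visit, or 97.5% under independence.

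**Reporting is not prescribed.** The protocol calls pairs below 0.05 significant. It does not say that each will be presented as a biological link, and no such claim is made here.

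**Conclusion.** The point holds for the rule as written. Judging 36 undifferentiated pairs at 0.05 each gives, when no association exists, a chance of at least one significant pair of 84% under independence and about 45–80% at assumed within-set correlations of 0.7 to 0.3. Repetition at the three postoperative visits, if done, raises this to about 77–99%. The figures assume 41 pooled patients, two-sided tests and no true associations. The within-set correlations and the number of visits are assumptions.

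The consequence is limited to the secondary, associational objective, so this is a change that should be made, not one on which the study's main comparison depends.

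**What to change.** In section 3.2 and the Statistics Plan:

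1. Exempt the correlation analysis from the blanket P<0.05 rule and label it exploratory.
2. Fix the family before the data are examined: which visits, that the surface measures enter as change from baseline, and whether patients are pooled or analysed by surgery group. Without this step the adjustment can be shaped after the results are known.
3. Report every coefficient in that family, with its 95% confidence interval, in one matrix.
4. Claim an association only if it passes Benjamini-Hochberg at 5% over the whole family.

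This takes a few sentences and needs no new patients, measurements or visits. The cost is that fewer correlations can be claimed, and more so the larger the family chosen, which is a reason to limit the visits to those of real interest.
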